### Power calculations

Power calculations were conducted with the G*Power software package [54]. In the clinical analysis (follow-up measures) the power for detecting group differences at *p* < .05 under the assumption of a medium effect size (Cohen’s d = .5) is 78% with two sample *t*-tests when treatment (*n* = 60) and control groups (*n* = 40) are pooled. Assuming an effect size of f = .61 as observed for the neurofeedback effect on VS reduction in our pilot study [18], the neurofeedback analyses based on an ANOVA repeated measures model with a group x time contrast has a power of 89% in the VS and of 88% in the rIFG to detect FWE (Bonferroni) corrected significant results in the respective ROI analyses.

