Participants who meet inclusion criteria are randomly assigned to one of five groups: three experimental and two control groups, respectively. Each group has to fulfil different tasks with either downregulating the ventral striatum, upregulating the right inferior frontal gyrus (rIFG), increasing the connectivity (negative correlation) between rIFG and VS, downregulating the auditory cortex (downregulation control) or upregulating the auditory cortex (upregulation control). The auditory cortex was chosen as control region because it is not involved in cue-reactivity [22].

Group allocation of included participants is conducted by the study team with a computer-generated random list based on the sequence of inclusion. No stratification factors are used in the allocation process.

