### Statistical analyses

As primary outcome analysis we will conduct group comparisons of relapse rates with survival analysis and assess reduction of alcohol intake during the follow-up phase. As secondary and exploratory outcome measures we will assess whether rtfMRI NFB reduces alcohol craving during the NFB sessions, how brain activation and brain connectivity changes within and between the sessions, whether functional or structural MRI markers can be identified that predict neurofeedback learning and the success of the intervention, and whether differences in efficacy of the group-specific interventions do exist.

To analyze the effects of rtfMRI NFB, offline data analysis will be conducted with MATLAB and SPM. Data preprocessing will consist of slice-time correction, realignment, segmentation of the anatomical image, normalization to the MNI space, smoothing, and identification of outlier volumes with excessive head motion. The preprocessed data will be used in first level single subject analyses in which the time courses of the experimental conditions will be convolved with the canonical hemodynamic response function and used in a general linear model to estimate brain responses during rtfMRI NFB. Then, first level results will be used in second level group comparisons to estimate differential activation between groups, test for associations with clinical variables, and assess the predictive value of imaging markers for the future course of the disease. Additionally, large-scale adaptations in functional networks during rtfMRI NFB will be assessed by whole-brain psychophysiological interaction analysis [53].

Depending on the type of the data, missing data will either be left out from the analyses (e.g. fMRI data), or imputed (e.g. missing questionnaire items).

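### The 78% power for the clinical comparison holds only for an undeclared one-sided 5% test; the ordinary two-sided test gives 68%

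*Protocol article*

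**What the plan says.** The Power calculations section of the protocol article reports that "Power calculations were conducted with the G*Power software package". For the clinical follow-up measures it gives "the power for detecting group differences at *p* < .05", "under the assumption of a medium effect size" (Cohen's d = .5), and states that this power "is 78% with two sample *t*-tests when treatment (*n* = 60) and control groups (*n* = 40) are pooled".

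The 60 and 40 follow from the design. N = 100 patients go to five groups, described under Screening assessment & group allocation as "three experimental and two control groups, respectively", so 60 against 40 is the pooled contrast with every randomised patient counted.

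The Statistical analyses section describes the primary analysis: "we will conduct group comparisons of relapse rates with survival analysis and assess reduction of alcohol intake" during follow-up. Neither section says whether any test is one- or two-sided.

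**The concern.** The power sentence supplies every input except the sidedness of the test. It speaks of group differences, which has no direction, and quotes an unqualified p < .05, which is conventionally read as two-sided. With the other inputs fixed, the two-sided calculation does not return 78%.

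Two things are at stake:

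- **If the analysis is two-sided**, the study is weaker on its main clinical question than the article says, and a null result would be taken as more informative than it is.
- **If the analysis is made one-sided to match the power figure**, the false-positive rate in the favourable direction is 5%, twice the 2.5% that a conventional two-sided 5% test allows.

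While sidedness stays open, the choice between the two could be made after the data are seen.

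**Working it through.** **Inputs**, all from the Power calculations section: two-sample t-test, d = 0.5, n₁ = 60, n₂ = 40, α = 0.05, stated power 78%. Sidedness is not given.

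**Formula.** For two independent means the test statistic follows a noncentral t distribution with

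- degrees of freedom: n₁ + n₂ − 2 = 60 + 40 − 2 = 98
- noncentrality: d × √(n₁n₂/(n₁ + n₂)) = 0.5 × √(2400/100) = 0.5 × 4.899 = 2.449

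Power is the probability that this variable exceeds the critical value. In the two-sided case the opposite tail is added; here it is negligible.

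**Reproducing the stated figure**

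| Test at α = 0.05 | Critical t (98 df) | Power |
|---|---|---|
| One-sided | 1.661 | 78.46% |
| Two-sided | 1.984 | 67.92% |

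The one-sided result rounds to the printed 78%. The two-sided result is 78 − 67.9 = 10.1 points lower. A normal approximation gives the same picture: 78.9% one-sided and 68.8% two-sided.

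**Could another two-sided calculation give 78%?**

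| Two-sided variant, d = 0.5 | Power |
|---|---|
| Wilcoxon test (relative efficiency 0.955), 60 vs 40 | 65.9% |
| Equal groups 50 vs 50, or F-test with f = 0.25 and N = 100 | 69.7% |
| 60 vs 60 | 77.5% |

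The last comes close, but it needs 120 patients and contradicts both the stated 60/40 split and N = 100. At 60 vs 40, a two-sided test reaches 78% only if α is raised to about 0.097, which is in effect a one-sided 5% test.

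**What two-sided 78% would require**

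- At 60 vs 40: d = 0.563 instead of 0.50.
- At d = 0.5 and a 3:2 split: between 125 patients (77.6%) and 130 patients (79.2%).

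**Type II error at d = 0.5.** Two-sided: 100 − 67.9 = 32.1%. Implied by the article: 100 − 78 = 22%.

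**Incomplete follow-up.** The article gives no expected loss, so the rates below are assumptions applied equally to both pooled groups.

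| Assumed loss | Evaluable | Two-sided power |
|---|---|---|
| 0% | 60 vs 40 | 67.9% |
| 10% | 54 vs 36 | 63.2% |
| 15% | 51 vs 34 | 60.7% |
| 20% | 48 vs 32 | 58.1% |

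**The case against.** The strongest reply is that nothing was miscalculated. The one-sided figure honours every stated input and rounds exactly to 78%. The aims are worded in a direction: the Background asks about beneficial effects, and the Statistical analyses section refers to reductions in alcohol intake and craving. A one-sided calculation may well have been intended, and a condensed article may leave sidedness to the full protocol. It follows that declaring and justifying a one-sided test would also be a coherent repair.

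This explains where the number came from, but it does not make the sentence correct as printed. A directional aim is not a declared one-sided test; most efficacy trials hope for benefit and still test two-sided. Nor is this only a missing detail, because the article prints a specific result that is about 10 points too high on the ordinary reading of its own wording.

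Two further objections stand in part:

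- **Relapse is to be compared by survival analysis.** Neither 22% nor 32% is therefore the type II error of that analysis. Both belong to a t-test on a continuous follow-up measure such as alcohol intake. The t-test is nevertheless the only power basis the article gives for its clinical question, so the figure should be right on its own terms.
- **The loss figures rest on assumed rates**, and a survival analysis would keep patients lost early as censored observations. They show how the t-test figure moves and are secondary to the main point.

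**Conclusion.** The concern holds. With the stated inputs (d = .5, 60 vs 40, p < .05, two-sample t-test), two-sided power is 67.9%, not 78%. The printed figure is reproduced only by a one-sided test at 5%, which the article never declares.

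The conclusion rests on reading an unqualified p < .05 for group differences as two-sided, and on taking the stated 60/40 split with all patients evaluable. It does not depend on the assumed losses, which would only lower the figure further. The point must be corrected, because this is the only power statement supporting the sample size for the clinical comparison.

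**What to change.** In the Power calculations section:

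1. State that the clinical comparison is tested two-sided at the 5% level.
2. Replace 78% by 68% for d = .5 with 60 vs 40 evaluable patients, or keep 78% and give the detectable effect as d = 0.56.
3. Add one line with the power under the loss to follow-up that the investigators expect.

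If a one-sided test was really intended, the article must say so, give its level and justify it before the final analysis.

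The cost is a sentence or two and a less favourable power figure. Recruitment, randomisation and study procedures do not change.

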For connectivity NFB, partial correlations between the intensity values of the VS and right IFG adjusted for the cerebro-spinal fluid signal over the last 15 volumes are used to calculate the feedback signal. Again, the scale of the feedback thermometer is adaptively adjusted to the maximum absolute value reached. In this exploratory group, the goal of the intervention is to increase the inhibiting influence of the rIFG to the VS and the participants are instructed to downregulate the depicted process. However, a negative correlation between VS and rIFG could arise from the desired state, but also from an inverse behavior of the system with increased VS and diminished frontal activity. To enforce the top-down inhibitory state of the system we included the additional constraints in the connectivity feedback that the VS should be downregulated and the rIFG should be upregulated and switch negative feedback values to positive if these constraints are not met.

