However, the results from Kirsch et al. [18] could also imply that a critical factor for the treatment effect could be whether patients get the impression that they are able to actively control their own brain response to alcohol cues. Since patients can assume that the intention of the training is the reduction of alcohol cue associated craving, they might apply strategies to reduce this craving and, accordingly, to downregulate the feedback signal. Kirsch et al. [18] showed that successful VS downregulation was accompanied by the application of specific cognitive strategies, which might have let to the concurrent increase of prefrontal activation, although this activation was not fed back to the participants. Thus, the direction of the signal modulation could be a critical point in NFB, and patients receiving the downregulation instruction might show more effects than those receiving the upregulation instruction.

Future studies could further elaborate the effect of instruction by converting the feedback signal in upregulation conditions and instructing all participants to downregulate the signal, which from our experience seems to be the natural direction expected by patients in a cue-reactivity addiction context. This would also allow blinding the patients completely, not only with respect to the group (experimental vs. control) but also the kind of regulation they are expected to apply.

The study could also reveal additional mechanistic information about the mode of action of rtFMRI NF. Importantly, we conduct fMRI scans with whole-brain coverage, which will allow us to investigate the role of other brain regions like amygdala, insula cortex, or ventromedial PFC which were not directly targeted with NFB in our study but play important roles alcohol-related cue-reactivity [23, 24].

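### The pooled 60 versus 40 contrast is unbalanced on instruction direction, so one sixth of any direction effect is counted as treatment effect

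*Protocol article*

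**What the plan says.** Under Screening assessment & group allocation, patients are "randomly assigned to one of five groups: three experimental and two control groups, respectively". Two experimental groups carry their direction in their name: ventral striatum (VS) down and right inferior frontal gyrus (rIFG) up. The third is the connectivity group; under Neurofeedback setup the article says of it that "the participants are instructed to downregulate the depicted process". The two controls both regulate the auditory cortex, one down and one up, and are labelled as the downregulation and the upregulation control.

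Power calculations gives "the power for detecting group differences at *p* < .05" for the follow-up measures "under the assumption of a medium effect size (Cohen’s d = .5) is 78" per cent, "with two sample *t*-tests", "when treatment (*n* = 60) and control groups (*n* = 40) are pooled". This is the only clinical treatment-control contrast that the article specifies. Statistical analyses names group comparisons of relapse by survival analysis, together with reduction of alcohol intake, as the primary analysis. It does not say which groups are compared, and it places differences between the group-specific interventions among the secondary and exploratory questions.

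The Discussion suggests that the direction of regulation may be critical and that "patients receiving the downregulation instruction might show more effects than those receiving the upregulation instruction". It does not connect this remark to the pooled contrast.

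**The concern.** Both directions occur in both pools, but in different proportions. Randomisation cannot even this out, because direction is part of what defines each arm. If being told to downregulate helps in itself, for instance because patients then use strategies that lower craving, the treated pool gains more from it than the control pool.

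The Discussion justifies the active controls on the ground that they make results specific to the targeted brain processes rather than to neurofeedback regulation as such. Two direction-specific controls serve that aim well. Pooling without regard to direction gives up the matching they provide, and the resulting error runs in favour of treatment if the Discussion's suggestion is right.

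**Working it through.** **Inputs.** Pool sizes 60 and 40, d = 0.5, significance level 0.05 and stated power 78% come from Power calculations. Sidedness is not stated. Directions come from Screening assessment & group allocation and Neurofeedback setup. Two inputs are assumptions: 20 per group (60/3 and 40/2), and a direction effect δ of 0.2 to 1.0 within-group SD, taken as equal for target and control regions.

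**1. The plan's own figure.** For a two-sample t-test with 98 degrees of freedom, the noncentrality is 0.5 × √(60 × 40/100) = 0.5 × √24 = 2.449. Power is 78.5% one-sided and 67.9% two-sided. The stated 78% is therefore reproduced only by a one-sided test, and both bases are shown below.

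**2. The imbalance.**

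| Pool | Told to downregulate | Told to upregulate | Share down |
|---|---|---|---|
| Treatment (60) | VS 20 + connectivity 20 | rIFG 20 | 40/60 = 2/3 |
| Control (40) | auditory-down 20 | auditory-up 20 | 20/40 = 1/2 |

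Expected pooled difference = region effect + δ × (2/3 − 1/2) = region effect + δ/6.

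**3. Effect on the pooled t-test with no region effect.** The rejection rates come from 400,000 simulated trials per value of δ, with fixed cells of 40, 20, 20 and 20.

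| Assumed δ (SD) | Spurious difference δ/6 (SD) | Share of planned d = 0.5 | Two-sided rejection | One-sided rejection |
|---|---|---|---|---|
| 0.2 | 0.033 | 7% | 5.2% | 6.8% |
| 0.5 | 0.083 | 17% | 6.1% | 9.9% |
| 1.0 | 0.167 | 33% | 8.7% | 15.4% |

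With direction in the model, rejection stays at 5.0% in every row, on either basis. An approximation that treats direction as a random mixture within each pool gives somewhat higher figures (5.3%, 6.8% and 11.3% two-sided). The fixed cells match this design better.

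**4. Price of adjustment.** The information on the treatment contrast is n₁n₂/(n₁ + n₂), summed over strata:

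- Unstratified: 60 × 40/100 = 24.
- Stratified: 40 × 20/60 + 20 × 20/40 = 13.33 + 10 = 23.33, a loss of 3%.

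The standard error rises from 1/√24 = 0.204 to 1/√23.33 = 0.207. Power at d = 0.5 falls from 78.5% to 77.4% one-sided, or from 67.9% to 66.7% two-sided.

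**The case against.** The pooling appears only in the power section, where it may be a simplification. The analysis section leaves the compared groups open, and strata or covariates of a survival model are details that an article may leave to a fuller document. The design already allows direction-matched comparisons, and the Discussion talks openly about direction. It also warns that group differences may reflect how hard the regulation is. This stands in part: a reader might infer that the unadjusted pool is the fixed primary analysis, and the article does not say so. But it is the only clinical treatment-control contrast given a definition and a power figure, so its composition is open to comment. The point concerns that composition and does not rest on an omitted covariate list.

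A reader might also infer that the authors expect direction to act on outcome whatever the target region. The text is more cautious: it speaks of what could be critical and what might happen, and it does not make that general claim. The size of the effect is therefore an assumption throughout.

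Finally, the leak is small. For direction alone to yield the planned 0.5 SD, δ would have to be 0.5 × 6 = 3 SD. The smallest two-sided significant difference is about 1.98 × 0.204 = 0.405 SD, which needs 0.405 × 6 = 2.4 SD, even before allowing for the wider spread that such an effect would cause within each pool. This stands, and it limits how strongly the point can be put.

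**Conclusion.** The imbalance is real and follows from the article's own description of the arms. The pooled contrast measures the region effect plus one sixth of any direction effect, and the article's own suggestion about direction would make that addition favour treatment.

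The bias is modest: negligible two-sided at an assumed 0.2 SD, about one percentage point of false-positive rate at 0.5 SD, and under four at 1.0 SD. On the one-sided basis that reproduces the stated power, the excess is about two, five and ten points.

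It would be tempting to conclude that a positive result could not be attributed to the targeted processes at all. The arithmetic does not support that; attribution is weakened, not lost.

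The conclusion rests on 20 patients per group, a direction effect common to target and control regions, and a t-test on a continuous outcome. Nothing was computed for the survival analysis, though the 2/3 versus 1/2 imbalance applies there too.

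**What to change.** If treatment and control groups are pooled for the clinical analysis, state that the comparison is stratified by instruction direction:

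- **Relapse:** a log-rank test or Cox model stratified on down/up, comparing VS plus connectivity with auditory-down, and rIFG with auditory-up, then combining the two strata.
- **Alcohol intake:** include direction as a factor in the model.
- **Unstratified pool:** report it as a secondary result.

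State the sidedness of the test in the same place, since the power figure depends on it.

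The cost is a sentence or two of text and about one percentage point of power on the t-test scale. Recruitment, arms and data collection are unchanged. The cost for the log-rank or Cox analysis would need its own calculation, with an assumed relapse rate.

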### Data management and dissemination

To ensure data quality, questionnaires are automatically scanned and entered into the study data base. Data management and monitoring is conducted by the study team. Study data will be stored on servers of the Central Institute of Mental Health separated from personal information of the participants. At the end of the study personal information will be deleted. The procedures comply with German data privacy laws. We will conduct interim analyses on the acquired data to present the study to scientific audiences (e.g. at conferences, meetings, etc.) during the data acquisition phase. Results of the final analyses will be published in scientific journals and presented on scientific conferences. Authorship will be defined in accordance to the German Research Foundation’s recommendations for safeguarding good scientific practice [55]. Study conduct is reported and audited in interim and final reports of the SyBil-AA consortium to the funding agency.

## Discussion

In the Systems Biology of Alcohol Addiction (SyBil-AA) rtfRMI NFB study we are assessing the efficacy of rtfRMI NFB on ventral striatal cue-reactivity and frontal control processes in the treatment of alcohol use disorder. To the best of our knowledge, the study is one of two ongoing clinical trials of rtfMRI NFB in AUD (see Cox et al. [56] for a description of the other trial), and will contribute to the understanding of the use of rtfMRI NFB as a clinical application in the context of a clinical treatment program for AUD.

Besides the primary goal of testing clinical effects, the study will provide data which will be useful to investigate how rtfMRI NFB is leading to changes in the brain, whether intervention success can be predicted by means of neurobiological signatures and clinical variables, and for which patients rtfMRI might be beneficial. Since we focus on ventral striatal activation to alcohol cues and its prefrontal control, it could be expected that particularly those patients will profit from the intervention that show substantial ventral striatal cue reactivity to alcohol cues prior to the intervention as it has been shown for other treatments before [57]. However, it has been shown that AUD is often associated with a shift of cue reactivity from ventral to dorsal striatum [58]. For those patients, showing a more habit like addiction behavior, instead of the ventral striatum, the dorsal striatum might be an interesting target for NFB interventions in AUD. Nevertheless, there is no doubt, that prefrontal control regions play a central role in craving and relapse [25]. Therefore, it could be speculated that patients receiving a PFC upregulation feedback might benefit from the NF treatment even if they do not show strong ventral but increased dorsal striatal activation to alcohol related cues.

An innovative condition in the present study is the connectivity feedback condition. It has been shown in the context of nicotine addiction that adding connectivity information to the feedback signal increases efficiency [49] and reduces cigarette craving but this has neither been shown for alcohol patients nor with respect a long-term outcome of a treatment.

However, the results from Kirsch et al. [18] could also imply that a critical factor for the treatment effect could be whether patients get the impression that they are able to actively control their own brain response to alcohol cues. Since patients can assume that the intention of the training is the reduction of alcohol cue associated craving, they might apply strategies to reduce this craving and, accordingly, to downregulate the feedback signal. Kirsch et al. [18] showed that successful VS downregulation was accompanied by the application of specific cognitive strategies, which might have let to the concurrent increase of prefrontal activation, although this activation was not fed back to the participants. Thus, the direction of the signal modulation could be a critical point in NFB, and patients receiving the downregulation instruction might show more effects than those receiving the upregulation instruction.

Future studies could further elaborate the effect of instruction by converting the feedback signal in upregulation conditions and instructing all participants to downregulate the signal, which from our experience seems to be the natural direction expected by patients in a cue-reactivity addiction context. This would also allow blinding the patients completely, not only with respect to the group (experimental vs. control) but also the kind of regulation they are expected to apply.

The study could also reveal additional mechanistic information about the mode of action of rtFMRI NF. Importantly, we conduct fMRI scans with whole-brain coverage, which will allow us to investigate the role of other brain regions like amygdala, insula cortex, or ventromedial PFC which were not directly targeted with NFB in our study but play important roles alcohol-related cue-reactivity [23, 24].

Another interesting aspect which might have an influence on the results is the type of control for neurofeedback (see e.g. [59]). We chose an active type of control in the NFB study in which participants from the control group receive a real feedback signal from a control region, which in our case is the auditory cortex that is not involved in cue-reactivity [22]. Other possibilities would be to use a control group without feedback, a group that just views feedback signal of other participants without instructions, or a yoke-control group that is told to regulate the process but receives feedback from another person. For task comparability we decided against the first two options, and for ethical reasons a yoke-control group in which participants would receive fake instructions is questionable. Our active-control groups will lead to results based on specific target brain processes, and not per se on brain regulation through NFB. However, differences between groups might still be related to differences in regulation difficulty.

There are some shortcomings of the protocol. First, the study is only single-blind. The staff members must prepare the individual feedback set up (definition of ROI, definition of direction) and are therefore not blinded. In future studies, a double-blind protocol could be implemented by separating staff that prepares the individual NF setup and staff that instructs the participants. However, we think it is worth to test the general applicability of rtfMRI NF to AUD patients before setting up such an extensive study protocol. Second, the study was retrospectively registered in the German Clinical Trials Register (DRKS00010253; WHO Universal Trial Number (UTN): U1111–1181-4218). Due to fast inclusion of the first patient, registration was conducted shortly after the begin of the study, but before any data was processed or analyzed (Inclusion of first patient: 03/30/2016; application for registration: 04/26/2016; registration date: 05/10/2016). However, the registration complies with the goals of the study described in the grant proposal and the study protocol will not be altered during the study. Finally, we have not defined stopping criteria, because we do not expect side effects besides those that can be expected from fMRI scanning, which is a safe and well-established technique. However, the principle investigators will decide whether to continue or terminate the study or specific parts of it if side effects were reported by the participants.

Overall, the study is well suited to provide valuable data on the efficacy of rtfMRI NFB as an add-on treatment for AUD in a clinical setting. Furthermore, the large amount of imaging data collected on the three scanning days will be helpful to better understand how rtfMRI NFB is working, and to identify factors that predict its clinical effects and could potentially be useful for developing personalized treatment approaches.

